## Methods

### Sample size determination

The sample size was estimated using G*Power version 3.1 (Heinrich Heine University Düsseldorf, Germany) based on the composite sarcopenia Z-score. A previous comparable trial reported a large intervention effect on sarcopenia Z-score (SMD = 1.40) [31]. With 80% power, a Bonferroni-adjusted two-sided α of 0.0167, and ANCOVA adjustment for baseline sarcopenia Z-score, 16 completers per group are required in an individually randomized design, corresponding to 64 completers in total. To account for cluster randomization at the residential-building level, the sample size was inflated using the adjusted design effect formula, DE = 1 + [m (1 + CV^2^) − 1] × ICC. Based on a recent cluster-randomized trial in senior care facilities using Short Physical Performance Battery (SPPB) as the primary outcome, an intracluster correlation coefficient (ICC) of 0.025 was adopted [32]. A CV of 0.30 was used to account for anticipated variation in cluster size [33]. With 19 clusters, these assumptions yielded an adjusted design effect of approximately 1.12. After allowing for a 30% dropout rate, the sample size was increased to 104 participants, targeting approximately 26 participants per group. Cluster effects will be further addressed using mixed-effects models with random intercepts for residential building and participant.

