### Outcome assessment

Outcome assessments are scheduled to evaluate both short-term intervention effects and the maintenance of longer-term benefits. With the exception of biospecimen collection, the outcomes will be assessed at baseline, weeks 12, 24, and 48, and again at 1-year and 2-year post-intervention follow-up. HG will additionally be measured every 4 weeks during the intervention period to capture more continuous changes in muscle strength, whereas biospecimens will be collected at baseline and week 48 only. The full assessment schedule is summarized in Table 1.

**Table 1 Tab1:** Schedule of study assessments

Measure	Screening	Baseline	Intervention												Follow-up	
		**Week 0**	**Week 4**	**Week 8**	**Week 12**	**Week 16**	**Week 20**	**Week 24**	**Week 28**	**Week 32**	**Week 36**	**Week 40**	**Week 44**	**Week 48**	**Year 1**	**Year 2**
Primary outcomes																
Sarcopenia Z-score	** × **	** × **			** × **			** × **						** × **	** × **	** × **
Components																
ASMI	** × **	** × **			** × **			** × **						** × **	** × **	** × **
HG	** × **	** × **	** × **	** × **	** × **	** × **	** × **	** × **	** × **	** × **	** × **	** × **	** × **	** × **	** × **	** × **
SPPB	** × **	** × **			** × **			** × **						** × **	** × **	** × **
Secondary outcomes																
TUG		** × **			** × **			** × **						** × **	** × **	** × **
PA level		** × **			** × **			** × **						** × **	** × **	** × **
sEMG		** × **			** × **			** × **						** × **	** × **	** × **
Balance function		** × **			** × **			** × **						** × **	** × **	** × **
Sample collection		** × **												** × **		
Questionnaires		** × **			** × **			** × **						** × **	** × **	** × **
Clinical events		** × **			** × **			** × **						** × **	** × **	** × **
Care-dependency		** × **			** × **			** × **						** × **	** × **	** × **

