### Statistical analysis

All analyses will follow the intention-to-treat (ITT) principle, including all randomized participants in their assigned groups regardless of adherence or withdrawal [75]. Data will be stored in a password-protected database and managed by designated research staff. Analyses will be performed by an independent statistician using R software (R Foundation for Statistical Computing, Vienna, Austria).

Baseline characteristics will be summarized using descriptive statistics. Continuous variables will be presented as mean ± SD or median [IQR], as appropriate, and categorical variables as frequencies and percentages. Baseline balance across groups and clusters will be descriptively assessed.

Primary and secondary continuous outcomes will be analyzed using linear mixed-effects models, with fixed effects for group, time, and group-by-time interaction, and adjustment for the baseline value of the corresponding outcome and relevant covariates where appropriate. Random intercepts for residential building clusters and participants will be included to account for cluster randomization and repeated measurements. The main intervention effect will be estimated from the group-by-time interaction, with Week 48 as the primary endpoint. Bonferroni-adjusted post-hoc comparisons will be conducted where appropriate. Binary or categorical outcomes, including adverse events, will be analyzed using generalized linear mixed models. Long-term clinical events and care-dependency records will be summarized descriptively by group, with exploratory cluster-adjusted analyses conducted if event numbers permit.

Model assumptions will be assessed using residual diagnostics, and transformations or robust methods will be considered if needed. Missing outcome data will be handled using multiple imputation under the missing-at-random assumption. Sensitivity analyses will compare the intention-to-treat results with per-protocol and complete-case analyses. Effect sizes will be reported as standardized mean differences for continuous outcomes and odds ratios for binary outcomes. Statistical significance will be set at a two-sided α = 0.05.

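### With repeated measurements handled only by random intercepts, the Week 48 standard error is misstated if correlation with baseline fades, by an amount that depends on visits the protocol does not name

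*Protocol article*

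**What the plan says.** The Statistical analysis section specifies linear mixed models "with fixed effects for group, time, and group-by-time interaction, and adjustment for the baseline value of the corresponding outcome". It then states how dependence is handled: "Random intercepts for residential building clusters and participants will be included to account for cluster randomization and repeated measurements". The Sample size determination section names the same two terms: "Cluster effects will be further addressed using mixed-effects models with random intercepts for residential building and participant". Neither section mentions a random slope, a visit-specific variance, serial correlation or a baseline-by-time term.

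The primary contrast is fixed as follows: "The main intervention effect will be estimated from the group-by-time interaction, with Week 48 as the primary endpoint". On timing, the Outcome assessment section says that "the outcomes will be assessed at baseline, weeks 12, 24, and 48, and again at 1-year and 2-year post-intervention follow-up". If weeks are counted from baseline, the two late visits fall at about weeks 100 (48 + 52) and 152 (48 + 104). The protocol does not say whether they enter the model that yields the Week 48 result.

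Two further sentences bear on the point. One is a general safeguard: "Model assumptions will be assessed using residual diagnostics, and transformations or robust methods will be considered if needed". The other concerns missing data: "Missing outcome data will be handled using multiple imputation under the missing-at-random assumption".

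**The concern.** A participant random intercept with independent residuals is a compound-symmetric model. It takes Weeks 12 and 24 to be as correlated as Week 12 and the 2-year visit, and it gives each visit the variance averaged over all fitted visits. The visits here are unequally spaced over roughly three years, in residents aged 75 and over.

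The model also adjusts for baseline. Baseline explains less of a later measurement if the correlation with it declines, so the variance left after adjustment would then rise from Week 12 to Week 48. A pooled variance would be too low for Week 48 if only earlier visits are pooled with it, and might be too high if later visits are pooled as well.

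At stake is the standard error of the primary effect, and with it the error rate of each of the three comparisons implied by the planning alpha of 0.0167. A standard error that moves with an unstated choice of visits also leaves room for that choice to be made after the data are seen.

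**Working it through.** **The plan's own figure.** The documents state no standard error, variance or within-person correlation for the Week 48 effect, so there is nothing to reproduce for the disputed quantity. The sample size does reproduce:
- Design effect: 1 + [(104/19) × (1 + 0.30²) − 1] × 0.025 = 1.124.
- Completers: 64 × 1.124 = 71.9, rounded up to 72.
- With 30% dropout: 72/0.70 = 102.9, rounded up to 103; 26 per group gives 104.

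No repeated-measures term enters this, so N is not touched by what follows.

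**Inputs.** The alpha levels are 0.0167 (Sample size determination) and 0.05 (Statistical analysis). The visits are those in the assessment schedule. The correlations with baseline, ρ, are assumptions.

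**Formula.** Take unit variance at each visit, complete data, and no building effect.
- Variance left after baseline adjustment at visit t: v(t) = 1 − ρ(t)².
- A single slope b, the mean of the ρ(t), adds (ρ(t) − b)².
- The random-intercept model uses the mean of v over the fitted visits.
- Model SE / true SE at Week 48 = √(mean v / v(48)).
- Actual error = 2[1 − Φ(z × ratio)], with z = 2.393 for 0.0167 and 1.960 for 0.05.

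**Weeks 12, 24 and 48 fitted** (the slope term is negligible here and left out):

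| Assumed ρ | v | Mean v | SE ratio | Error at 0.0167 | Error at 0.05 |
|---|---|---|---|---|---|
| 0.90/0.85/0.75 | 0.190, 0.278, 0.438 | 0.302 | √(0.302/0.438) = 0.83 | 0.047 | 0.10 |
| 0.80/0.78/0.75 | 0.360, 0.392, 0.438 | 0.396 | √(0.396/0.438) = 0.95 | 0.023 | 0.06 |
| No fading | equal | equal | 1.00 | 0.0167 | 0.05 |

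**All five visits fitted** (slope term included, because it is no longer negligible; the late correlations are further assumptions):
- 0.90/0.85/0.75, then 0.65/0.55: b = 0.74, mean v = 0.452, v(48) = 0.438, ratio 1.02, error 0.015 at 0.0167.
- 0.90/0.85/0.75, then 0.60/0.50: b = 0.72, mean v = 0.482, v(48) = 0.438, ratio 1.05, error 0.012.
- 0.80/0.78/0.75, then 0.70/0.65: b = 0.736, mean v = 0.458, v(48) = 0.438, ratio 1.02, error 0.014.
- The steeper pattern followed by 0.65/0.60 gives a ratio of exactly 1.00. Slower late fading than that leaves the standard error slightly too small.

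**A different shape: serial decay, ρ(t) = r^(t/48).**
- r = 0.8: ratio 0.78 on Weeks 12–48 (error 0.061) and 1.09 on five visits (0.009).
- r = 0.6: ratio 0.81 (0.053) and 1.03 (0.013).

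**Simulation with this trial's features.** This used 19 clusters, ICC 0.025, and assumed staggered dropout reaching 30% at Week 48, with 600 replicates and three contrasts each. Where correlation decayed:
- Weeks 12–48 gave SE ratios of 0.80–0.91 and error of 0.038–0.068 at a nominal 0.0167.
- Five visits gave ratios of 1.00–1.04 and error of 0.015–0.023.

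Under true compound symmetry the ratio was 1.04 for either visit set, with error of about 0.019.

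**Simulation of the alternative.** With 4 arms of 18, complete data, no building effect, and baseline correlation falling from 0.84–0.90 at Week 12 to 0.70–0.77 at Week 48, the random-intercept model on Weeks 12–48 ran at 0.032–0.039. A visit-specific analysis ran at 0.016–0.021.

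**The case against.** The best defence is that the protocol does not fix the residual covariance. A random intercept can sit alongside autocorrelated or heteroscedastic residuals, and an article commonly leaves that detail to the analysis plan. This stands in part: nothing says that the residuals are independent, so the point holds on the ordinary reading and not by necessity. But the protocol is not silent. It names its device for repeated measurements, twice, and that device is the two intercepts. That is a stated choice which can be improved.

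The safeguard on model assumptions is also real, since unequal variance by visit is something residual diagnostics can show. Protection is only partial, because no trigger and no method are named. Multiple imputation does not help, because it leaves the covariance of the analysis model as it was.

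A reader might infer more than the documents support:
- That the Week 48 standard error is definitely wrong. No correlation is given, and without fading it is correct.
- That variance after baseline adjustment must grow. That is plausible, but it is an assumption.
- That the test is too liberal when all visits from Week 12 to 2 years are fitted. In the cases tried for that set the error was small, and mostly on the conservative side. The material understatement belongs to Weeks 12–48 alone.
- That clustering is ignored. A building intercept is included, although it does not relax the equal-variance and equal-correlation constraint within participants.

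**Conclusion.** The point holds in conditional form. As ordinarily read, the stated model is compound symmetric over unequally spaced visits with a single baseline slope, and the visits behind the primary result are not named. If correlation with baseline fades and only Weeks 12–48 are fitted, the Week 48 standard error is about 5–17% too small across the two assumed patterns, with error of about 0.023–0.047 against 0.0167. Steeper serial decay takes the shortfall to about 22%. With the two follow-up visits added, it is about right or slightly too large (about 0.012–0.015, and 0.009 under the steepest five-visit case). With no fading there is no error.

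All of this rests on assumed correlations. The closed-form figures also assume complete data and no building effect, though the simulation with clustering and dropout points the same way. The change is worth making because it is cheap and removes the dependence on an unstated choice, not because harm has been demonstrated.

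**What to change.** State in the analysis plan that:
- the primary model uses Weeks 12, 24 and 48;
- an unstructured within-participant residual covariance (one variance per visit, free correlations) replaces the participant random intercept;
- the baseline coefficient may differ by visit (baseline-by-time);
- the building random effect is kept, with a small-sample degrees-of-freedom correction suited to 19 clusters;
- a simpler heterogeneous-variance structure is the named fallback if the model does not converge;
- the 1- and 2-year visits are analysed in a separate or extended model.

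The cost is wording, plus four more within-participant covariance parameters: three variances and three correlations (6), against one participant variance and one residual variance (2). That should be estimable with about 104 participants. The sample size and data collection do not change.

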During weeks 1–12, specialists will provide on-site supervision for all sessions alongside caregivers. During weeks 13–24, on-site supervision will be reduced to one randomly scheduled visit per week, with the remaining sessions supported remotely. During weeks 25–48, sessions will be primarily supervised by caregivers using the video-guided materials, while specialists continue to provide remote oversight. Attendance at each scheduled exercise session will be recorded electronically by caregivers and summarized as an adherence and feasibility indicator; detailed attendance definitions and calculation procedures are provided in Additional file 1.

Adherence support will be guided by the Capability, Opportunity, Motivation–Behaviour (COM-B) model [40], and the Theoretical Domains Framework (TDF) [41] targeting exercise adherence in participants. Specifically, delivery within participants’ residential buildings, small-group sessions, caregiver assistance, and specialist supervision will target physical and social opportunity; health education, video-guided instruction, and seated exercise formats will target psychological and physical capability; and attendance monitoring, supportive feedback, low-value attendance-based incentives, and public recognition of highly engaged participants who consent to being acknowledged will target reflective and automatic motivation through reinforcement, self-efficacy, social norms, commitment, and habit formation [42].

Intervention sessions may be modified or temporarily discontinued for individual participants in the presence of acute illness, pain exacerbation, dizziness, chest discomfort, marked fatigue, participant refusal, or any other condition judged by caregivers or supervising staff to make continued exercise unsafe. Participants who discontinue the intervention will be encouraged to remain in outcome assessments whenever possible. Detailed intervention procedures are presented in Fig. 2 and Additional file 1.

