The composite sarcopenia Z-score will be calculated separately by sex based on AWGS 2019. The three standardized deficit components will be summed, with higher scores indicating greater sarcopenia severity. Sex-specific baseline standard deviations will be used for standardization.Muscle mass (ASMI):ASMI will be measured using BIA with an InBody 770 device (InBody, Seoul, Korea). Participants will be instructed to remove shoes and socks, stand upright on the device, and maintain an upright posture with arms slightly abducted. Measurements will be performed under standardized conditions, including fasting for at least 4 h and emptying the bladder prior to assessment.Muscle strength (HG):HG will be measured using a calibrated Jamar hydraulic hand dynamometer (Patterson Medical, USA). Participants will be seated with the elbow flexed at 90°, forearm in neutral position, and wrist slightly extended. Each hand will be tested three times with a 1-min rest between trials, and the maximum value across all six trials will be recorded in kilograms.Physical performance (SPPB):Physical performance will be evaluated using the Short Physical Performance Battery (SPPB), which includes three components: GS test, 5STS test, and balance tests (side-by-side, semi-tandem, tandem). Each component will be scored from 0 to 4 according to standard criteria, with a total SPPB score ranging from 0 (worst) to 12 (best). Assessments will be performed by trained staff following standardized protocols, and participants will be allowed a single practice trial before formal measurements.

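### The primary effect is taken from the group-by-time interaction of a baseline-adjusted model; if baseline is only a covariate, that term is not the Week 48 treatment effect

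*Protocol article*

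**What the plan says.** The Statistical analysis section analyses the primary outcome with "linear mixed-effects models, with fixed effects for group, time, and group-by-time interaction", and with "adjustment for the baseline value of the corresponding outcome and relevant covariates where appropriate". On the random part it says: "Random intercepts for residential building clusters and participants will be included to account for cluster randomization and repeated measurements". The quantity that decides the trial is then named: "The main intervention effect will be estimated from the group-by-time interaction, with Week 48 as the primary endpoint".

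Under Outcome assessment, "the outcomes will be assessed at baseline, weeks 12, 24, and 48, and again at 1-year and 2-year post-intervention follow-up". The section does not say which of these visits are responses in the model, whether baseline is one of them, or which visit is the reference.

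The Sample size determination section plans on a different quantity, a between-group difference adjusted for baseline: with "ANCOVA adjustment for baseline sarcopenia Z-score, 16 completers per group are required", at a two-sided alpha of 0.0167 and a standardized difference of 1.40. The composite is a deficit score, "with higher scores indicating greater sarcopenia severity", so a benefit is a negative difference.

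**The concern.** In a model with group, time and their product, the product term measures how the group difference changes between visits. It equals the treatment effect at Week 48 only if the group difference at the reference visit is zero in expectation. Randomization gives that at baseline but not at Week 12, after twelve weeks of exercise.

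Adjusting for baseline as a covariate usually means that baseline is not a response, which makes Week 12 the first visit in the model. A benefit that is present at Week 12 and kept to Week 48 would then give a primary estimate of zero, and one that partly wanes would appear as harm. Such profiles are possible here, because specialist support is tapered. All sessions are supervised on site in weeks 1–12, then "During weeks 13–24, on-site supervision will be reduced to one randomly scheduled visit per week", and supervision is remote from week 25. The same model serves every continuous outcome, so the problem is not confined to the Z-score.

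**Working it through.** **1. The planned quantity.** Inputs from Sample size determination: SMD 1.40, alpha 0.0167, power 80%, ICC 0.025, CV 0.30, 19 clusters, 30% dropout.
- Assumed conversion (not stated in the article): f = 1.40/√8 = 0.495. A four-group ANCOVA F test with 3 numerator df and one covariate needs N = 63, rounded to 64, or 16 per group. Power at 64 is 81%.
- m = 104/19 = 5.47; DE = 1 + (5.47 × 1.09 − 1) × 0.025 = 1.124.
- 16 × 1.124 rounds up to 18; 18/0.7 rounds up to 26; 4 × 26 = 104.

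The plan's figures are reproduced, and they rest on a baseline-adjusted group difference, not on an interaction.

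**2. Reading A: baseline as covariate only, responses from Week 12, Week 12 as reference.** Let d(t) be the adjusted difference from control at visit t.
- Group term = d(12).
- Group-by-Week-48 term = d(48) − d(12).
- Week 48 treatment effect = group term + group-by-Week-48 term = d(48).

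This is an identity. For scale, 300 two-arm trials were simulated per profile. The assumptions, not in the article, were 18 completers per arm, SD 1, within-person correlation 0.6, five buildings per arm, data with ICC 0.025, and a fit with a participant intercept only. Rejection is at 0.0167.

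| Assumed d(12) → d(48) | Expected interaction | Simulated interaction | Result |
|---|---|---|---|
| −1.4 → −1.4 | 0.00 | −0.01 | interaction rejected 2%; Week 48 contrast −1.39, rejected about 100% |
| −0.7 → −1.4 | −0.70 | −0.69 | interaction rejected 47% |
| −1.6 → −1.0 | +0.60 | +0.61 | wrong sign; Week 48 contrast −0.98, rejected 92% |
| 0 → −1.4 | −1.40 | −1.41 | equals the Week 48 effect |

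**3. Reading B: baseline is also a response row and the reference time.** The interaction is the between-group difference in change from baseline to Week 48. For the same four profiles, in the same order, the simulated means are −1.39, −1.42, −0.99 and −1.39, against true Week 48 effects of −1.4, −1.4, −1.0 and −1.4. The term is on target.

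The baseline covariate does not vary over time, so it cancels from a within-person change. With r the correlation between baseline and Week 48:
- change-score variance ∝ 2(1 − r); ANCOVA variance ∝ 1 − r²; ratio = 2/(1 + r).
- r = 0.5: 1.33; r = 0.7: 1.18; r = 0.8: 1.11.

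In the simulation the empirical SD was 0.29–0.30 for this term, against 0.26–0.28 for the adjusted Week 48 contrast.

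Power of the change-score comparison at SMD 1.40 and alpha 0.0167, with 18/1.124 ≈ 16 effective per arm (t test): 92% at r = 0.5, 97% at 0.6, and above 99% at 0.7 and 0.8.

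**The case against.** The strongest reply is that the sentence can be read benignly. It names Week 48, the section reports standardized mean differences and provides for Bonferroni-adjusted comparisons, and the sample size assumes a baseline-adjusted difference. All of this fits an analyst who fits group by time and then takes group contrasts at Week 48. Under reading B even the bare coefficient is a valid effect. Model coding is also often left to an analysis plan, and none is shown here.

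Much of this stands. The article does not commit the authors to a Week 12 reference, and the efficiency loss under reading B is harmless at the planned effect. The effect profiles above are assumptions, since the article gives no trajectory. Continued sessions and progressive loading make growth as plausible as waning, and in the late-onset profile the coefficient is correct.

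What does not stand is the appeal to missing detail. The article goes beyond leaving the contrast open: it says which term carries the main effect, and in the usual baseline-adjusted set-up that term is the wrong one. A later plan that follows the sentence literally would inherit the error.

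A reader might go further in three ways that the article does not support:
- That the interaction is never the Week 48 effect. Reading B shows that it can be.
- That a joint interaction test is the primary test. None is written. If one were used, it would have 6 df (12 with Years 1 and 2) under reading A and 9 or 15 under reading B.
- That on-site supervision ends after Week 12. It is reduced then and becomes fully remote from week 25.

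**Conclusion.** The concern holds conditionally. The stated rule does not fix the primary estimand. Under the usual set-up for a baseline-adjusted model, its literal form gives the change in effect between Week 12 and Week 48. That quantity can be zero or reversed when exercise is better than control at Week 48, and it is not what the trial was sized on. This follows from the algebra; only the illustrative sizes rest on assumed profiles, correlation and completers.

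Under the other set-up the estimate is valid. The cost is a variance 1.1 to 1.3 times that of ANCOVA for assumed correlations of 0.8 to 0.5, without power falling below 80% at SMD 1.40. Two analysts could both follow the text and reach opposite primary conclusions, so the sentence should be replaced before unblinding.

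**What to change.** Replace the sentence with one that states:
- the responses are the post-baseline Z-scores, with the visits that enter the model listed;
- the baseline Z-score and its interaction with time are covariates (or, as an alternative, a constrained longitudinal model with a common baseline mean is used);
- the primary estimate is the adjusted difference between each exercise group and control at Week 48, that is, the group term plus the Week 48 interaction;
- each of these three comparisons is tested at the Bonferroni-adjusted two-sided 0.0167 of the sample size section. The analysis section now gives only a general 0.05, with adjusted post-hoc comparisons where appropriate.

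The change costs one or two sentences before unblinding. It needs no new data, and the sample size stays at 104.

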Although substantial clinical evidence supports the effectiveness of exercise in the management of sarcopenia, much of this evidence has been generated under highly controlled experimental conditions, with limited consideration of implementation in real-world settings such as nursing homes [28]. This gap between efficacy and applicability has prompted calls for a shift in research priorities, emphasising the optimisation of exercise prescriptions and the promotion of long-term adherence [29]. In institutional care environments, intervention success depends not only on clinical efficacy but also on operational feasibility, safety, and the capacity to sustain participant engagement. Accordingly, effective programmes are those that can capitalise on existing facilities and staff resources, minimise dependence on specialised equipment or external expertise, and integrate smoothly into routine care workflows [30].

Against this background, the present pragmatic trial evaluates a caregiver-led exercise programme that integrates modified Baduanjin with resistance training in oldest-old nursing home residents with sarcopenia. Using a cluster-randomised design and multimodal assessment, the study examines the comparative effectiveness of these interventions while simultaneously exploring underlying biological mechanisms and implementation feasibility. By prioritising practicality and sustainability, this programme is intended to provide an exercise framework that can be readily adopted by other long-term care facilities facing similar resource constraints and resident needs.

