### Study design and setting

The SCOPE study (Sarcopenia Care in Oldest-old: a Pragmatic Exercise cluster-randomized controlled trial) is a pragmatic cluster-randomized controlled trial, aimed at evaluating the real-world effectiveness and feasibility of different exercise interventions for sarcopenia in nursing home residents aged 75 and above. A total of 104 participants will be randomized into one of four groups: (1) Control Group (CON), (2) Modified Baduanjin Group (MBG), (3) Resistance Training Group (RTG), and (4) Combined Exercise Group (CEG).

A flow diagram of the trial is presented in Fig. 1. The SCOPE study will begin with continuous screening for sarcopenia following the Asian Working Group for Sarcopenia (AWGS) 2019 criteria [34]. Older adults clinically diagnosed with sarcopenia and meeting the eligibility criteria will be enrolled. After a standardized 30-min health education session and subsequent randomization, participants will undergo a 48-week pragmatic group-based exercise intervention within their residential buildings. This pragmatic intervention will be delivered by trained, familiar caregivers using video materials recorded by exercise specialists, with a phased reduction in researcher supervision over time: full on-site supervision during week 1–12, a hybrid model combining on-site and remote supervision during week 13–24, and fully remote supervision during week 25–48. Outcome assessments will be conducted at baseline, week 12, week 24 and week 48, with additional follow-up evaluations at 1 year and 2 years post intervention to examine the maintenance of long-term effects.

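### The Bonferroni alpha of 0.0167 used for the sample size is not carried into the analysis rule, so control of family-wise error for the primary outcome is not fixed

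*Protocol article*

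**What the plan says.** Sample size determination plans for 80% power at "a Bonferroni-adjusted two-sided α of 0.0167", taking a previous trial that "reported a large intervention effect on sarcopenia Z-score (SMD = 1.40" as its basis, and concludes that "16 completers per group are required in an individually randomized design, corresponding to 64 completers in total". It does not name the comparisons behind the adjusted alpha.

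Study design and setting has three exercise arms and one control: "A total of 104 participants will be randomized into one of four groups".

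Statistical analysis contains three statements that bear on the decision rule:

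- On the source of the primary estimate: "The main intervention effect will be estimated from the group-by-time interaction, with Week 48 as the primary endpoint".
- On multiplicity, its only sentence: "Bonferroni-adjusted post-hoc comparisons will be conducted where appropriate".
- On the level, at the end of the section: "Statistical significance will be set at a two-sided α = 0.05".

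That section does not repeat 0.0167 and gives no number of comparisons. The Background adds, as a general aim, that "the study examines the comparative effectiveness of these interventions".

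**The concern.** The two sections can lead to different verdicts on the same result. Suppose one exercise arm differs from control at Week 48 with p = 0.03. Under the sample-size criterion (0.0167) that is not a positive finding. Under the analysis section it can be, because the main effect comes from the interaction, significance is set at 0.05, and Bonferroni attaches only to comparisons called post-hoc, and only where judged appropriate.

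With four groups and control as reference, the group-by-time interaction at Week 48 consists of three arm-versus-control terms. Nothing in the text says those terms are the post-hoc comparisons that get adjusted. At stake is the claim that any exercise programme works on the primary outcome.

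This is more than detail that a condensed article leaves to an analysis plan. The article states a multiplicity-adjusted criterion when justifying its size, and then states a decision rule that does not contain it.

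**Working it through.** **Inputs from the protocol article.** Four arms with equal target sizes; planning alpha 0.0167 two-sided; analysis alpha 0.05 two-sided; 80% power; SMD 1.40; 16 completers per arm before cluster inflation.

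**Step 1. Reproduce the planning alpha.**
0.05/3 = 0.01667, which rounds to 0.0167. 0.05/6 = 0.0083, which does not match. Planning therefore used three comparisons. Four arms give 3 comparisons with control, or 4 × 3/2 = 6 pairwise comparisons.

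**Step 2. Family-wise error under each reading.**
The family-wise error is the probability that at least one contrast satisfies |z| > z(1 − α/2). It was simulated with 2,000,000 draws of four independent arm means of equal variance, no true differences, and z = (difference of two means)/√2. The Bonferroni bound is k × α for k contrasts.

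| Reading | Simulated | Bound k × α |
|---|---|---|
| Three versus control, each at 0.0167 | 4.4% | 3 × 0.0167 = 5.0% |
| Three versus control, each at 0.05 | 12.5% | 3 × 0.05 = 15% |
| Six pairwise, each at 0.0083 | 4.2% | 6 × 0.0083 = 5.0% |
| Six pairwise, each at 0.0167 | 7.9% | 6 × 0.0167 = 10% |
| Six pairwise, each at 0.05 | 20.3% | 6 × 0.05 = 30% |

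The first row is 4.4% or 4.5% depending on the run. As a cross-check on the second row, three independent tests would give 1 − 0.95³ = 14.3%; sharing one control lowers this to 12.5%.

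**Step 3. Would an overall test first repair it?**
Calling the comparisons post-hoc might mean that a 3-df test at 0.05 comes first. With that gate and then three unadjusted comparisons with control:

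- All arms equal: 4.0%.
- One arm truly effective, taken here as SMD 1.40 with 16 per arm: the gate almost always opens, and the chance of a false claim for one of the two ineffective arms is 9.1%.

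A gate would protect only when nothing works.

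**Step 4. Does the size of the family affect power?**
Two-group noncentral t power at 16 per arm, SMD 1.40, with no covariate gain and no clustering:

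- alpha 0.0167: 92%
- alpha 0.0083: 86%

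Both exceed the planned 80%. The SMD detectable with 80% power is 1.20 at 0.0167 and 1.31 at 0.0083, both below the planned 1.40.

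**The case against.** The strongest reply is that the two sections state one rule twice. If 0.05 is the family-wise level and Bonferroni-adjusted p-values are compared with it, three comparisons give 0.0167 per test, which is the planning figure. That is an ordinary reading and may well be what the sponsor means. It stands as a possible reading, but the text does not say it, and the words limiting the adjustment to post-hoc comparisons where appropriate leave it optional.

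A reader might infer three stronger conclusions. The document does not support them.

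- *That family-wise error is not controlled.* Bonferroni applied to the family actually tested holds 5% for three or for six contrasts. The fault is that its application is not fixed. The 12.5% and 20% figures describe uncorrected testing, which the text permits but does not prescribe.
- *That three versus six comparisons is wholly open.* The planning alpha fixes three. The case for six rests on a general sentence of aim in the Background, which is not a list of hypotheses. The count is unstated only in the analysis section.
- *That six comparisons would leave the trial short of power.* On the plan's own effect size, pairwise power remains 86%. An overall four-group ANCOVA test run at 0.0083 could need more completers (72 rather than 64, if f = 1.40 × √(1/8) = 0.495), but the article does not state that test.

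It is also fair that a list of secondary contrasts and the labelling of exploratory tests can be left to an analysis plan. The level and the adjustment for the primary outcome are different, because the article states both and they do not match as written.

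**Conclusion.** The point holds as a gap between two stated rules. The article sizes the trial on three comparisons at 0.0167, and its analysis section neither names those comparisons nor makes the adjustment binding. For the three comparisons with control, the family-wise error is about 4.5% or 12.5% depending on which section is followed; about 20% is the upper end and needs all six pairs to be tested without correction.

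These figures assume equal arms, a large-sample normal approximation and no true differences, and they treat arm means as independent. The small number of buildings per arm is a separate matter and is not included. The planned sample size is not called into question here.

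**What to change.** In Statistical analysis:

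1. Name three primary contrasts: each exercise arm versus control on the sarcopenia Z-score at Week 48.
2. State that two-sided 0.05 is the family-wise level for these three.
3. Make the adjustment mandatory, by Holm or Dunnett, and remove the discretionary wording for this family. Both are at least as powerful as Bonferroni for three comparisons with control. Holm keeps 0.0167 as its first step (then 0.025 and 0.05).
4. Report exercise-versus-exercise contrasts as secondary estimates with confidence intervals, which serves the comparative aim in the Background without enlarging the confirmatory family.
5. In Sample size determination, say that 0.0167 refers to the same three contrasts.

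The change is wording only and leaves 104 participants as planned. The cost is a stricter criterion than 0.05 for any single comparison taken alone, which is the criterion the trial was sized for. It should be settled before any outcome data are seen by arm.
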